### Sample size {14}

Considering an alpha risk of 5% and a beta risk of 10%, and assumptions of a rate of patients with a clinically relevant decrease in FIQ of 50% in the Immediate solution group, versus 25% in the Delayed solution group, the number of subjects needed for a comparison of proportions is 77 per group (154 in total). Considering a 10% risk of loss to follow-up, the number of 85 patients per group will be retained (170 patients in total). The clinically relevant decline retained is 14% on the FIQ scale [29].

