### Trial design {8}

This multicenter superiority trial is randomized into two parallel groups of the type of “Immediate solution” versus “Delayed solution.” The main interest in that design is to limit the disappointment bias, each group has access to the solution: one immediately on the day of randomization, the second group after 3 months, once the primary objective is assessed. The allocation ratio between the two groups is 1:1.

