## Statistical methods

### Statistical methods for primary and secondary outcomes {20a}

Descriptive analyses will be expressed by means − standard deviations and medians − interquartiles for quantitative data, as well as numbers and percentages for qualitative data.

The analysis of the primary endpoint will be performed using a Fisher exact test. For secondary endpoints at M3, all endpoints evaluating a change in score between D0 and M3 will be analyzed via bivariate linear regressions, considering the randomization group and the value of the score at D0. Qualitative criteria will be analyzed using a Fisher test. The secondary endpoint 8 is descriptive and will follow indications for descriptive analysis. For secondary endpoint 9, since analysis considers several measurement points with different states, mixed regressions (linear or logistic depending on the type of variable) will be implemented. Data at M6 from the delayed intervention group will be analyzed for comparison at M3 via a McNemars test (test of proportions for paired data).

These analyses are planned in two stages: (i) all criteria evaluated at 3 months will be performed when all patients have made their follow-up visit at M3 and (ii) all criteria evaluated at 6 and 9 months will be analyzed when the follow-ups at M9 of all patients are completed.

The results will be presented in accordance with the recommendations of the CONSORT Statement. These analyses will be implemented after a consistency check and a freeze of the database, in accordance with the good practices of the Grenoble Alps University Hospital. The software used will be Stata 15 or a more recent version (StataCorp LLC).

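### The 77 per group fits an uncorrected chi-square-type test; under the planned Fisher exact test, power at the planned evaluable size is about 87–89%, not 90%

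*Protocol article*

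**What the plan says.** Sample size {14} sets alpha at 5% and beta at 10%, with assumed responder rates "of 50% in the Immediate solution group, versus 25% in the Delayed solution group". It concludes that "the number of subjects needed for a comparison of proportions is 77 per group (154 in total". It then adds an attrition allowance: "Considering a 10% risk of loss to follow-up, the number of 85 patients per group will be retained", or 170 in all. Neither the formula nor the test behind the 77 is named, and sidedness is not given.

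Trial design {8} describes a superiority trial and states: "The allocation ratio between the two groups is 1:1".

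Statistical methods {20a} does name the test: "The analysis of the primary endpoint will be performed using a Fisher exact test".

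**The concern.** The sizing and the analysis are both stated firmly, and they do not belong to the same test. Fisher's exact test is conditional and discrete, so at these group sizes its real type I error lies well below the nominal 5%, and it loses power against the uncorrected chi-square test. If the 77 came from a formula for the latter, the declared beta risk does not describe the analysis that will be run.

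At stake is the trial's only power statement. A reader who faces a non-significant primary result would rely on a false-negative risk of 10% that the named test does not give at the planned evaluable size.

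**Working it through.** **Inputs.** p1 = 0.50, p2 = 0.25, alpha = 0.05, power = 0.90, 77 evaluable and 85 enrolled per group, 10% loss (all Sample size {14}); 1:1 allocation (Trial design {8}); Fisher's exact test (Statistical methods {20a}). Two-sided testing is inferred: the one-sided pooled formula gives 63, and 71 with continuity correction, so a one-sided design does not explain 77.

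**Step 1: reproduce the 77.** Pooled normal formula without continuity correction, with mean rate 0.375:

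n = [1.960 × √(2 × 0.375 × 0.625) + 1.2816 × √(0.25 + 0.1875)]² / 0.25² = 76.7, rounded up to 77.

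Other two-sided formulas:

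| Formula | n per group |
|---|---|
| Pooled, uncorrected | 76.7 → 77 |
| Arcsine | 76.7 → 77 |
| Unpooled | 73.6 → 74 |
| Continuity-corrected (approximates Fisher) | 85 |

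The stated 77 is thus correct for an uncorrected chi-square-type comparison. It is not a size for Fisher's test.

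**Step 2: exact power of the named test.** For every pair of responder counts, the two-sided Fisher p-value is the summed probability of all tables with the same margins that are no more probable than the observed one. Power is the sum of the binomial probabilities of the pairs with p ≤ 0.05, at 50% versus 25%. The same enumeration was done for the uncorrected chi-square test.

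| Evaluable, Immediate/Delayed | Fisher power | Chi-square power |
|---|---|---|
| 76/76 | 87.0% | 90.2% |
| 77/76 | 88.5% | 89.8% |
| 76/77 | 89.3% | 89.8% |
| 77/77 | 87.6% | 90.6% |
| 80/80 | 88.3% | 91.1% |
| 80/81 | 90.3% | 91.7% |
| 83/82 | 90.2% | 92.2% |
| 84/84 | 89.6% | 92.4% |
| 84/85 | 91.5% | 92.8% |
| 85/85 | 90.1% | 92.6% |

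Fisher power does not rise smoothly. Exactly equal arms make the test most discrete, so arms that differ by one patient often do better than a slightly larger balanced pair.

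**Step 3: power under the planned loss.** 85 × 0.90 = 76.5 evaluable per group. Over 76–77 per group Fisher power is 87.0–89.3%, so beta is 10.7–13.0%. If each patient is lost independently with probability 10%, and the Fisher power of each resulting pair of group sizes is weighted by its binomial probability, the average is about 88.4%.

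**Step 4: real type I error at 77/77.**

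| Common responder rate | Fisher | Uncorrected chi-square |
|---|---|---|
| 25% | 3.3% | 5.0% |
| 37.5% | 3.6% | 5.3% |
| 50% | 3.0% | 4.5% |

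This is the source of the power difference.

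**The case against.** The best defence is that the gap is small and depends on loss. The section on participant retention {18b} expects very few patients to be lost, because the primary questionnaire can be completed online without a visit. With nearly complete data from 85 per group, Fisher power is about 90%, as declared. Fisher's test also guarantees control of the type I error, which the uncorrected chi-square test does not quite do, and one to three points of power are small beside the uncertainty in the assumed 50% and 25%. All of this stands, and it limits the severity. It does not remove the mismatch: the sample size section itself plans for 10% loss and attaches the 10% beta risk to 77 per group, and at that size the named test falls short.

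Three stronger readings are tempting and are not supported.

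- A reader might infer, because the continuity-corrected formula gives 85 and 85/85 is the first equal-arm size to reach 90%, that the loss allowance is entirely used up and that 90% requires every enrolled patient to be evaluable. The enumeration contradicts this: 80/81 gives 90.3% and 83/82 gives 90.2%.
- A reader might infer an arithmetic error in the 77. There is none; it reproduces exactly under two standard formulas.
- A reader might make something of 85 against 86. Dividing gives 77/0.9 = 85.6, while multiplying gives 77 × 1.10 = 84.7. That is one patient per group and only a rounding remark.

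**Conclusion.** The point holds as a minor inconsistency between the sample size and the primary analysis. At the planned evaluable size the named test has about 87–89% power (87.6% at 77/77, about 88.4% averaged over random 10% loss), so the beta risk is about 11–13% instead of 10%. With little loss, power returns to about 90% or slightly above.

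This rests on the protocol's own responder rates, on two-sided testing (inferred), on the usual two-sided definition of Fisher's p-value, and, for the average, on independent loss at the same rate in both arms. The mismatch cannot inflate false positives and does not bias the estimated effect. It affects only how the power statement and a negative result should be read.

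**What to change.** No patients need to be added; Trial status reports that inclusions have ended. Choose one of two.

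1. **Keep Fisher and correct the power statement.** Say that 77 per group was derived for an uncorrected comparison of two proportions, that testing is two-sided (if that is so), and that exact power under Fisher's test is about 87–89% at 76–77 evaluable per group, rising to about 90% if few patients are lost. This costs one sentence and a slightly less favourable figure.

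2. **Align the test with the sizing.** Make the uncorrected chi-square test primary and keep Fisher as a sensitivity analysis. Exact power is then 90.2% at 76/76 and 90.6% at 77/77 (89.8% when the arms are 76 and 77). The cost is a type I error that can reach about 5.3%, and a formal change of primary test after enrolment. It must be documented before the three-month database freeze and before anyone has seen results by group. The article does not say whether that freeze has already taken place; if it has, only the first option remains.

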### Recruitment {15}

Each of the eight centers, renowned for their implication in fibromyalgia expertise and research, estimated its potential for inclusion based on their active patient file already followed within their center and on the availability of human resources (coaches and CRA). Thus, we reach an estimated recruitment of 230 patients over 12 months, which allows us to guarantee the inclusion of 170 patients in 12 months. The main limitation to patients’ recruitment is not the identification of eligible patients but the availability of coaches to provide coaching sessions at D0, D7, M1, and M2.

## Assignment of interventions: allocation

### Sequence generation {16a}

The randomization list includes random blocks of two different sizes. The block sizes were chosen to be small, to prevent group imbalance in the case of an early interruption of the study. The randomization is stratified by center and on the two levels of fibromyalgia severity assessed by the score on the FIQ questionnaire at inclusion day: moderate form (i.e 39 ≤ FIQ score < 59) or severe form (FIQ score ≥ 59) [29].

### Concealment mechanism {16b}

The randomization is performed using the Interactive Web-Response System module of Clininfo (Clininfo SAS – Lyon France - http://www.clininfo.fr/) which is an online central randomization service directly integrated into the eCRF. This platform is available 24h/24 and is compliant with the FDA 21 CFR part 11. Access to this randomization tool is only possible with a coach profile on the eCRF. For each coach of the study, a profile is created, and a login and password are provided by the Remdee Labs datamanager.

The following patient information will be uploaded to Clininfo eCRF before accessing the randomization button: first name and surname initials to create the patient; inclusion and exclusion criteria; Fibromyalgia Impact Questionnaire completed by the patient before inclusion. The score of this questionnaire is automatically calculated on the eCRF and used as a stratifying variable for the randomization. Then the coach clicks on the randomize button and the patient's group is displayed on the computer screen.

### Implementation {16c}

The randomization list has been generated before the start of the trial by a biostatistician of the Grenoble Alps University Hospital data engineering unit. Patients are included in the study by the investigating physicians during a medical consultation. Following this consultation, patients are referred to the coach who enters the data listed above into the eCRF (if the physician has not done this) and then performs the randomization.

## Assignment of interventions: Blinding

### Who will be blinded {17a}

Physicians are blinded to the randomization group while the coach and the patient know it. To guarantee the blindness of the physician, only the coach may randomize the patient and physicians can’t see the patient group on the eCRF. At each follow-up visit, the patient meets the coach first and then the physician. At the M3 visit, the coach reviews the first 3 months of use of the solution for the Immediate group and conducts the first coaching session for the Delayed group patient. So, this ensures patients from both groups have the wristband with them for consultation with the physician. The coach reminds the patient to keep quiet about his group during the consultation with the physician.

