Coaching is key to improve patient adherence to the technology and to increase compliance and effectiveness of the treatment. Coaching is provided by CRA, psychologists, or nurses from each clinical center, specifically trained by a neuropsychologist before the beginning of the inclusions. Four coaching sessions are realized from the delivery of the wristband:At D0 (or M3), upon delivery of the wristband, the patient is trained to use the wristband and the application and is informed about endorphins and their effects in the body. Recommendations for scheduling sessions are made according to the patient’s main symptoms.At D7 (or M3+7 days), a phone call is made to ensure that the patient has no difficulties in using the device, that they have drawn up a routine to use it and to answer questions.At M1 (or M4) and M2 (M5): a phone call, during which an assessment is made of the patient’s usage and impressions of change on their condition. If necessary, the coach provides advice on when and how often to use the wristband.

To standardize the three phone calls, coaches follow dedicated questionnaires that guide the exchange and address the technical aspects, the frequency and habits of use of the patient, the effects felt, ... To evaluate the autonomy of the patient over the following months, coaching does not continue beyond 3 months after patients have started using their wristband.

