#### Delayed solution description

The “Delayed solution” group consists of (i) from D0 to M3—3 months with the standard of care, *ii) from M3 to M6—3 months with the solution add to the standard of care, and (iii) from M6 to M9—3 months with the wristband and Fibrepik App in addition to the standard of care.

To avoid disappointment and lack of investment in the study by the Delayed group, we chose to provide the solution to this group after the collection of the main objective. The fact that these fibromyalgia patients could not benefit from the proposed innovative solution but only continue their usual treatment would have led to many patients refusing to participate or withdrawing consent. Since fibromyalgia is a long-term chronic disease, the 3-month delay for the Delayed solution group to benefit from the solution seems to be a very short period and perfectly acceptable.

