### Participant timeline {13}

Each patient participates in the study for a period of 9 months. The patient benefit from a consultation with the physician on the day of inclusion at D0 and then during three follow-up visits at 3 (M3), 6 (M6), and 9 (M9) months (Table 1). During each consultation, the outcomes listed above are collected. Randomization is performed by the coach at D0 and if the patient is in the Immediate solution group, he gives the wristband to the patient and performs the first coaching session. For the Delayed solution group, the delivery of the wristband and the first coaching session are performed at 3 months. For both groups, the coach conducted the three other coaching sessions by telephone after 7 days, 1 and 2 months of wristband’s use. A follow-up booklet is given to the patient at D0. The patient must report on it at the end of each week their consumption of drug and complementary treatments. One week per month, the patient indicates each day the pain score on a VAS. At the end of each month, he indicates the activity carried out during the month as well as the medical and paramedical consultations he has received.

**Table 1 Tab1:** Study schedule of enrolment, follow-up, and assessments

Name of the visit	Eligibility screen	Enrolment	Follow-up			Phone calls							
Temporality	D0–3W	D0	M3	M6	M9	D7	M1	M2	M3+7D	M4	M5	M7	M8
Time window for the visit	± 2W		[− 1W/+ 2W]			±2D	± 1W		±2D	± 1W			
Location of the visit	By phone	Pain center											
Information	✓	✓											
Informed consent		✓											
Clinical examination^a^		✓	✓	✓	✓								
Urine HCG if necessary		✓											
Questionnaires^b^		✓	✓	✓	✓								
Randomization		✓											
Collection of adverse events			✓	✓	✓	✓I	✓I	✓I	✓D	✓D	✓D	✓ID	✓ID
Personalized coaching^c^		✓I	✓D			✓I	✓I	✓I	✓D	✓D	✓D		
Reminder to complete the follow-up booklet							✓D	✓D		✓I	✓I	✓ ID	✓ ID

*M* month, *W* week, *D* day

^a^Clinical examination: height, weight, PAS, PAD, and pain on VAS

^b^Questionnaires: FIQ/PSQI/HAD/IMF20/EQ 5D-5L/GPAC/PGIC and CGIC (not at D0)

^c^Personalized coaching: in each box, it is specified for which group(s) it is realized. *I* Immediate solution, *D* Delayed solution

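### The M3 visit order allows the Delayed group's FIQ to be completed after wristband handover and first coaching, against the stated rule that the solution follows the primary assessment

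*Protocol article*

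**What the plan says.** Three places in the protocol article state that controls are assessed before they receive the solution. Trial design {8} gives it to "the second group after 3 months, once the primary objective is assessed". The Delayed solution description says "we chose to provide the solution to this group after the collection of the main objective". The Discussion repeats this for the primary endpoint at 3 months.

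The operational sections describe the visit as follows:

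- Who will be blinded {17a}: "At each follow-up visit, the patient meets the coach first and then the physician". At M3 the coach reviews the first 3 months of use with Immediate patients and "conducts the first coaching session for the Delayed group patient". The stated purpose is physician blinding: "So, this ensures patients from both groups have the wristband with them for consultation with the physician".
- Solution description: "At D0 (or M3), upon delivery of the wristband, the patient is trained to use the wristband and the application", with information about endorphins. The section on the choice of comparators gives this interview one hour.
- Participant timeline {13}: "For the Delayed solution group, the delivery of the wristband and the first coaching session are performed at 3 months". Of the physician consultations at D0, M3, M6 and M9 it says "During each consultation, the outcomes listed above are collected".

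The FIQ is self-administered on paper or through the patient's own eCRF access ({18a}). Home completion is encouraged (Discussion) but not required.

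**The concern.** The primary comparison is Immediate versus Delayed on the proportion with at least a 14% fall in FIQ from D0 to M3. It assumes that the Delayed M3 value is a pre-solution value. If a Delayed patient answers the FIQ after the coach meeting, that patient has just received an awaited device and heard its expected effects. An Immediate patient in the same slot has just gone over 3 months of use with the coach. The influences differ by arm and come immediately before a self-report by patients who know their group.

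A second analysis depends on the same value: {20a} plans a McNemar test of Delayed M6 against Delayed M3. The other M3 self-reports (PSQI, HAD, MFI-20, EQ-5D-5L, PGIC) have the same gap in timing.

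**Working it through.** **Step 1: the order implied for each M3 measure.**

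| M3 measure | How it is taken | Position relative to handover in the Delayed arm |
|---|---|---|
| FIQ and other self-questionnaires | Patient, paper or eCRF, clinic or home ({18a}, {18b}, Discussion) | Not fixed: before if done at home ahead of the visit; after if done in the consultation as {13} reads |
| CGIC | Not self-administered ({18a}); clinician rating | After |
| Visit VAS | Part of the clinical examination (Table 1, note a) | After |
| Weekly average VAS | Daily entries in the home booklet, one week per month ({13}) | Little affected by the visit order |

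**Step 2: is there a rule elsewhere that settles the first row?** At D0 there is. Under {16b} the FIQ is completed before inclusion and is in the eCRF before the randomization button can be used. No equivalent condition is stated at M3. {18b} notes that the FIQ can be entered on the eCRF if the patient cannot attend, which makes remote completion possible but does not place it before the coach.

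**Step 3: the planned sample size.** Inputs from {14}: 50% versus 25%, alpha 5% (taken as two-sided), power 90%, 1:1 allocation. Pooled-variance formula, mean proportion 0.375:

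n = [1.960 × √(2 × 0.375 × 0.625) + 1.2816 × √(0.5 × 0.5 + 0.25 × 0.75)]² / 0.25²
= [1.960 × 0.6847 + 1.2816 × 0.6614]² / 0.0625
= (1.3419 + 0.8477)² / 0.0625 = 76.7, so 77 per group.

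This matches the plan. 77 × 1.10 = 84.7 gives the stated 85; 77 / 0.90 = 85.6 would give 86, a trivial difference. The point changes neither figure.

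**Step 4: illustration of what a shift in the Delayed rate would do.** If a fraction f of Delayed FIQs follow the handover, and response among those rises by d, the arm-level shift is f × d. The documents give neither f nor d. With 77 per group and 50% in the Immediate arm:

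| Delayed rate | Arm-level shift (assumed) | Power, normal approximation | Power, Fisher exact |
|---|---|---|---|
| 25% | 0 (plan) | 90.1% | 87.6% |
| 30% | +5 points | 72.1% | 67.5% |
| 35% | +10 points | 46.9% | 41.0% |
| 20% | −5 points | 98.0% | 97.0% |

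The last row is a shift in the other direction. These rows show sensitivity; they do not estimate a bias.

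**The case against.** The best defence is that {17a} orders only the coach and the physician, to protect physician blinding, and does not mention the FIQ. Because the FIQ is self-administered, the sequence FIQ, coach, physician fits {8}, {17a}, the Delayed-group description and the Discussion all at once. The conflict then rests on one general sentence in {13}, which cannot be fully literal, since the listed outcomes include booklet entries, step counts and wristband logs. A full protocol, not shown, may contain the detailed sequence.

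Much of this stands. A reader might infer that the control arm's primary outcome is in fact measured after treatment has begun. The documents do not support that: they leave the order open, and home completion before the visit avoids the problem. A reader might also take the power figures as the expected loss. They are not, because the shifts have no source, and FIQs completed before the visit would be untouched. Same-day exposure also has limited room to move items with a recall period, such as the PSQI (past month) or the FIQ day counts. The visit window of up to +2 weeks adds no exposure, because handover takes place at the same visit.

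What the defence does not remove is the mismatch between sections. The article itself sets out the visit order, and that order as written permits what three other sections rule out.

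**Conclusion.** The point holds as an unresolved inconsistency over when the M3 FIQ and the other self-questionnaires are completed relative to coach contact. For the CGIC and the visit VAS, the stated order clearly places measurement after handover.

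The size is unknown. It depends on the share of M3 FIQs completed after the coach meeting and on the reaction of unblinded patients. A true device effect within one visit is unlikely; the mechanism is expectation or demand. The direction is also unknown: hope in the Delayed arm would dilute the difference, while demand in the Immediate arm would enlarge it. It would go too far to say that the primary result is biased in a given direction or that power falls to a given value.

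**What to change.** State in {13} and {17a} that, in both arms, the FIQ and the other M3 self-questionnaires are completed and entered before any M3 coach contact; the coach session follows, and the blinded physician visit comes last. This reconciles the text with {8}, the Delayed-group description and the Discussion. It keeps the coach-then-physician order and the blinding, and needs no extra visit.

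The text change alone probably comes too late for the data. Inclusion ended on 1 April 2022, so M3 fell by 1 July and, with the 2-week allowance, by about 15 July 2022, before publication on 5 September 2022. For visits already done:

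1. Use the eCRF audit-trail times described in {19}, and dates on paper forms where they exist, to classify each M3 FIQ as completed before coach contact, after it, or at an unknown time.
2. Report these shares by arm.
3. Add a sensitivity analysis of the primary endpoint that excludes or imputes FIQs completed after contact. Report it whatever the share, and do not make it depend on the 5–20% missing-data range that {20c} sets for multiple imputation.

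The cost is data handling and one extra analysis. The weakness is that the audit trail records when data were entered, not when a paper form was filled in, and the article mentions no recorded time of coach contact. The unknown category may be large and the analysis incomplete.

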#### Immediate solution description

The “Immediate solution” group consists of (i) from D0 to M3—3 months with the solution (wristband, Fibrepik App, and coaching) in addition to the standard of care, (ii) from M3 to M6—3 months with the wristband and Fibrepik App in addition to the standard of care, and (iii) from M6 to M9—3 months with the standard of care. These 3 last months with the standard of care is to evaluate the reminiscence effects of the millimeter waves.

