In secondary outcomes 6 to 9, we evaluated:6.Impression of the disease change at M3 by the patient on the Patient Global Impression of Change (PGIC) scale and by the caregiver on the Clinician Global Impression of Change (CGIC) scale7.Solution and wristband objectives: Frequency of use of the wristband on the 6-month period of use it. The frequency of use is an extract of the wristband log file; Usability of the wristband on the modular evaluation of key Components of User Experience (meCUE) questionnaire at M6 for patients of the Immediate solution group and at M9 for patients of the Delayed solution group; Solution satisfaction questionnaire (questionnaire created by the sponsor) at M6 for patients of Immediate solution group and at M9 for patients of Delayed solution group8.Number, description, and classification (serious/non-serious) of adverse effects9.Primary outcome and secondary outcomes 1 to 6 evaluated at 6 and 9 months.

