### Procedure for unblinding if needed {17b}

Not applicable. This study is on simple blinding: physicians do not know the group while coaches and patients are unblinded.

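### Physician blinding is declared without a time limit, but the step that equalises visible device status is described for M3 only, so a physician-rated CGIC at M9 cannot be assumed blinded

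*Protocol article*

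**What the plan says.** The section on who is blinded (item 17a) states: "Physicians are blinded to the randomization group while the coach and the patient know it". The section on unblinding (17b) repeats it: "physicians do not know the group while coaches and patients are unblinded". Neither gives a time limit.

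Item 17a lists four measures:

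- Allocation is hidden: "only the coach may randomize the patient and physicians can’t see the patient group on the eCRF".
- Visits follow a fixed order: "At each follow-up visit, the patient meets the coach first and then the physician".
- At M3 the coach reviews device use with Immediate patients and gives Delayed patients their first coaching session, at which the wristband is handed over: "So, this ensures patients from both groups have the wristband with them for consultation with the physician".
- The coach asks patients not to disclose their group to the physician.

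The two arms are then treated differently after M6. The Immediate solution description gives that group, from M6 to M9, "3 last months with the standard of care". The Delayed solution description gives the other group, over the same period, "3 months with the wristband and Fibrepik App in addition to the standard of care".

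CGIC is part of secondary outcome 6. Item 9 in the Outcomes section reads: "Primary outcome and secondary outcomes 1 to 6 evaluated at 6 and 9 months". Note b to Table 1 places CGIC at every visit except D0, that is at M3, M6 and M9.

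**The concern.** The authors treated a visible wristband as a threat to blinding at M3 and arranged the visit to remove it. The same threat returns at M9, in reverse: the Delayed group is on the device and the Immediate group has been off it for three months. The article describes nothing comparable for that visit, yet its blinding statement covers it.

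The M9 comparison is the one meant to show whether any effect persists after the waves stop. A clinician who can tell who is on and who is off the device may rate change in line with expectation, and the direction of that bias cannot be settled from the documents. The statistical methods section (20a) sends secondary outcome 9 to mixed regressions over several measurement points, so M9 ratings would be modelled together with M3 and M6 ratings as if all were obtained under the same conditions.

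**Working it through.** The article gives no figure to reproduce on this point. The check sets assigned device use by arm beside the blinding measures and the CGIC schedule.

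| Visit | Immediate, preceding 3 months | Delayed, preceding 3 months | Device-equalising step described? | Does device status separate the arms in the consultation? | CGIC collected? |
|---|---|---|---|---|---|
| M3 | on (full solution) | off, but handed the wristband by the coach before the consultation | yes | no, both carry one | yes |
| M6 | on (wristband and app) | on (full solution) | none described | no, both have used it since M3 | yes |
| M9 | off (standard care) | on (wristband and app) | none described | yes | yes |

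The other measures, taken one by one at M9:

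1. **Masking in the eCRF.** It applies at every visit. It hides the recorded allocation, not a device on the wrist or talk of using it.
2. **Coach before physician.** It applies at every follow-up visit. It creates an opportunity to equalise appearance, and at M3 that opportunity is used. The order alone equalises nothing.
3. **Reminder to keep quiet.** Its wording is not restricted to M3. It concerns the patient's group. A patient can respect it and still mention having stopped, or still using, the wristband. At M9 that tells a physician who knows the design which arm the patient is in.

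**Who rates CGIC.** The Outcomes section attributes the rating to the caregiver. The section on outcome collection (18a) says only that CGIC and the physical activity questionnaire are not self-administered. That the blinded physician rates it follows from the scale's name and is not stated. If the coach rates it, the rating is unblinded at every visit, because the coach knows the group.

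**Extent.** CGIC is rated at 3 visits, and the gap is shown at 1 of them. The primary endpoint is the patient's own FIQ at D0 and M3, so it does not depend on physician blinding.

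**Timing.** The Trial status section dates inclusions from November 15, 2021 to April 1, 2022. Adding 9 months puts M9 visits between about August 15, 2022 and January 1, 2023, before the visit window. The article is dated September 5, 2022, so at publication most of that M9 period still lay ahead.

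**The case against.** The strongest reply is that this is a journal article. Device collection and coach instructions at M6 and M9 belong in the full protocol, which is not shown, and an article may leave them out. The article also does not say that Immediate patients hand the wristband back at M6, so they might still carry one at M9. The coach-first order already allows devices to be dealt with before the consultation. Nothing in the statistical methods relies on physician blinding, and the Discussion concedes that the trial is not double-blind and points to patient self-report.

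Much of this stands, and it rules out several stronger readings that a reader might infer:

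- **That blinding is protected only at M3.** Masking in the eCRF and the visit order apply throughout, and the reminder is not limited to M3.
- **That CGIC at M6 is compromised too.** Both arms have been on the device since M3. The inference needs Immediate patients to surrender it to the coach before seeing the physician at M6, and the article describes no such step.
- **That CGIC at M9 is definitely unblinded.** What patients bring and say at M9 is not stated. Blinding there is unsupported, which is less than shown to be broken.
- **That CGIC is declared to be the trial's blinded outcome.** No section links physician blinding to CGIC or to any other outcome.

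The appeal to omitted detail does not dispose of the M9 point. The article states a property without limit, and its own treatment schedule removes the condition that supported that property at M3. A plan followed as written leaves the M9 claim without support.

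**Conclusion.** The point holds for M9 only. At that visit current device use tracks the randomised arm, no described measure conceals it, and a physician-rated CGIC cannot be assumed blinded. This rests on three assumptions: that the physician rates CGIC, that patients broadly follow their assigned device use from M6 to M9, and that the physician can see or hear about current use. If the coach is the rater, the blinding statement does not cover CGIC at any visit.

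The size is small: one late time point of one secondary outcome. Given physician rating, CGIC at M3 keeps its described protection, no problem is shown at M6, and the primary endpoint is untouched. The likely bias in the M9 ratings cannot be quantified from the documents.

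**What to change.** - For M9 visits still to come, have every patient in both arms leave any wristband with the coach before the physician's consultation. The coach is already seen first, so the visit order does not change.
- Extend the coach's reminder so that patients avoid mentioning current device use as well as their group.
- State who rates CGIC.
- Where these steps were not taken, report CGIC at M9 as not assuredly blinded, and limit the blinding statement so that it does not cover M9.

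The cost is a brief instruction to coaches, one or two sentences in the report, and a slightly less favourable description of the blinding. Sample size, the primary analysis and the visit schedule do not change.
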